### 2.3. Participants

Participant recruitment will be conducted from November 2025 to July 2026. Eligible participants aged 18–60 years must have a T1DM duration of more than one year and suboptimal glycemic outcomes, defined as HbA1c of 7.0–14.0% within the past three months or 14-day CGM-derived TIR < 70% within the past month. Participants will be excluded if they had recent episodes of diabetic ketoacidosis, concurrent severe gastrointestinal diseases, significant gastrointestinal surgery, pregnancy, or lactation. The diagnosis of T1DM adheres to the criteria established by the World Health Organization and the American Diabetes Association. Full criteria are listed in Table 1.

**Table 1 pone.0343078.t001:** Inclusion and exclusion criteria for enrollment.

Inclusion Criteria	
1	T1DM was diagnosed by an endocrinologist for at least 1 year
2	Aged 18–60 years (inclusive)
3	HbA1c between 7.0 to 14.0% (within past 3 months) or TIR < 70% (14-day CGM within the past month)
4	On MDI or insulin pump therapy for ≥3 months
5	TDD before admission ≥0.3 IU/kg/day, with a basal rate ≥0.05 IU/hour
6	Women of childbearing age are willing to use appropriate contraceptive measures
7	Signed informed consent form

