#### 2.4.3. Randomization and blinding.

Following the completion of the run-in period, eligible participants will be randomized in a 1:1 ratio to either the intervention or the control group. Randomized allocation sequences will be generated using a permuted block design in R software. Sequentially numbered, opaque, sealed envelopes will be prepared and stored by a non-investigational team member. To minimize selection bias, the randomization codes are assigned by an independent researcher. Once an eligible participant is enrolled, the principal investigator notifies the independent researcher to open sequentially the sealed envelope for allocation. yFMT and placebo capsules are identical in appearance, shape, odor, and specifications.

The investigational capsules will be assigned predefined random codes that were dispensed without selection. Randomization number is not allowed to be reassigned following participant discontinuation. The randomization code will be securely maintained by an independent statistician throughout the study. The code will remain inaccessible to investigators, participants, and endpoint assessors, except for authorized access by the independent Data Monitoring Committee (DMC) during the pre-specified interim analysis. Full unblinding will occur only after database lock and completion of the final analysis.

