### 2.9. Sample size and pilot trial rationale

This is a pilot study. The primary objectives are to assess the feasibility (recruitment, adherence) and safety of the oral yFMT, to evaluate the preliminary effciency, and to collect preliminary effect-size estimates for the planning of a subsequent pivotal trial.

As no prior data exist on achieving the composite glycemic target (TIR > 70% with TBR3.9 < 4%) following yFMT in adults with T1DM, a traditional sample size calculation based on an anticipated effect size was not feasible. The sample size for this trial was therefore determined in accordance with methodological best practices for pilot trial design. We referenced the guidance proposed by Wang et al., which indicates that a pilot study for a future definitive trial with 90% power and a two-sided alpha of 0.05 typically requires approximately 10–25 participants per group to provide meaningful parameter estimates for small-to-moderate effect sizes [23]. Based on this, and considering the common requirement for assessing primary feasibility objectives (e.g., recruitment rate, procedural acceptance), a sample size of 10 participants per group was set.

A pre-planned interim analysis will be conducted after the first 10 participants (50% of the total planned sample) have completed the 12-week follow-up. During this interim analysis, the DMC will review unblinded data, including safety outcomes and the primary composite endpoint, to evaluate safety and obtain preliminary treatment effect estimates for future sample size planning. No formal hypothesis testing will be performed, and no sample size re-estimation is planned for the current trial, consistent with its pilot nature. Based on the DMC’s review, the trial may continue as planned, be modified, or be terminated early if unacceptable safety concerns or clear futility are observed.

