For the primary efficacy endpoint assessed from baseline to Week 12 post-intervention, a generalized estimating equation (GEE) model with a binary distribution, logit link function, and an exchangeable correlation structure will be employed. The model includes group, time, and their interaction as fixed effects, with baseline composite achievement status as a covariates, as appropriate. Given the pilot nature of the study (n = 20), Fisher’s exact test will additionally be performed at each time point as a sensitivity analysis to ensure robustness. For continuous secondary outcomes, linear mixed-effects models will be applied with group, time, and their interaction as fixed effects, the baseline value of the respective outcome as a covariate, and age and T1DM duration as additional covariates, with a random intercept for each participant. Multicollinearity will be assessed using the variance inflation factor (VIF), with VIF > 10 indicating significant collinearity. Given the limited sample size, a parsimonious sensitivity model including only baseline value, group, and time will also be performed to assess robustness against overfitting. Feasibility outcomes will be assessed descriptively. All feasibility endpoints will be presented as frequencies and percentages, with 95% confidence intervals where appropriate. For secondary continuous outcomes and covariates, missing data will be addressed using multiple imputation. Twenty imputed datasets will be generated using baseline outcome values, age, T1DM duration, and treatment group as predictors, and results will be pooled using Rubin’s rules. Logistic regression analysis will be used to explore factors associated with response to yFMT treatment. CGM metrics, as recommended by international expert consensus, will be calculated using Glyculator 2.0 software (Medical University of Lodz, Poland). All statistical analyses will be performed using R software (version 4.3.2) and GraphPad Prism 9.0. Statistical significance is defined as two-sided *P* < 0.05. Bonferroni correction will be applied for multiple comparisons in post hoc analyses.

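### As worded, the primary GEE can put baseline status on both sides of the model, and with 10 per arm it may often give no finite Week 12 effect estimate

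*Protocol article*

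**What the plan says.** Section 2.5 and Table 3 define the primary endpoint as a change from the run-in CGM window to Weeks 10–12 in the proportion meeting both CGM targets. The primary analysis in section 2.10 begins "For the primary efficacy endpoint assessed from baseline to Week 12 post-intervention, a generalized estimating equation (GEE) model", with a logit link and exchangeable correlation. The terms follow: "The model includes group, time, and their interaction as fixed effects, with baseline composite achievement status as a covariates, as appropriate". Because of the small sample, Fisher's "exact test will additionally be performed at each time point as a sensitivity analysis to ensure robustness". Section 2.10 also counts missing primary assessments as non-response. It does not say which analysis becomes primary if the GEE cannot be estimated.

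Section 2.9 states that "a sample size of 10 participants per group was set" and lists preliminary effect-size estimates for a later pivotal trial among the primary objectives. Entry under Table 1 requires "HbA1c between 7.0 to 14.0% (within past 3 months) or TIR < 70% (14-day CGM within the past month" range.

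**The concern.** Two features of the primary model work against each other.

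- If baseline is a level of time, the group-by-time term compares Week 12 with baseline on the log-odds scale. It then needs at least one achiever and one non-achiever in each arm at baseline as well as at Week 12. Ten participants per arm, selected for suboptimal control, may not supply that.
- If baseline status is also a covariate, it partly predicts itself in the baseline rows. That distorts the interaction even when the model can be fitted.

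The result at stake is the one the pilot is meant to hand on. An infinite or inflated odds ratio cannot be used to plan the next trial, and a replacement chosen after unblinding would not be prespecified.

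**Working it through.** **Inputs from the document.** Ten per arm (section 2.9); 1:1 allocation (section 2.4.3); two-sided 0.05 (section 2.10); model terms as quoted.

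**Inputs that are assumed.** The document gives no achievement rates. Ranges used: baseline 5-30%, Week 12 placebo 10-30%, Week 12 yFMT 30-50%, latent within-person correlation 0.5.

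**The plan's own figures.** The counts agree: 2 × 10 = 20, and the interim at 10 is 10/20 = 50%. Ten is the lower end of the cited guidance, "a pilot study for a future definitive trial with 90% power and a two-sided alpha of 0.05 typically requires approximately 10–25 participants per group". The 90% belongs to the future trial, so there is no power figure to reproduce here.

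**Step 1: empty baseline arm, baseline as an outcome level.** If one arm has 0/10 at baseline, its baseline log-odds can fall without limit while every other fitted cell stays the same, so group-by-time has no finite estimate. Adding the covariate does not prevent this. For baseline rate p,

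P(at least one arm 0/10) = 1 − [1 − (1 − p)^10]²

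- p = 5%: 1 − (1 − 0.599)² = 84%
- p = 10%: 1 − (1 − 0.349)² = 58%
- p = 20%: 1 − (1 − 0.107)² = 20%
- p = 30%: 1 − (1 − 0.028)² = 6%

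**Step 2: sparse Week 12 cells counted as well.** Trials were simulated under the assumed ranges, and each was checked for whether the Week 12 interaction has a finite logit estimate. With baseline as both outcome and covariate, it had none in about 89-93% of trials at baseline 5%, 64-77% at 10%, 30-57% at 20% and 12-45% at 30%. A repeat with 300 trials per scenario gave 86-93%, 69-79%, 30-52% and 11-46%, so the ranges carry a few points of simulation error.

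**Step 3: what the software shows.** Take baseline 1/10 placebo and 0/10 yFMT, and Week 12 1/10 and 4/10. An exchangeable GEE on baseline and Week 12 gave an interaction of 34.3 with no computable standard error (no covariate), and 25.2 with standard error 144 (with covariate). Convergence was reported both times, so the failure can pass unnoticed. The same Week 12 counts give a difference of 40% − 10% = 30 percentage points. With Wilson limits 1.8% to 40.4% for 1/10 and 16.8% to 68.7% for 4/10, the Newcombe interval is:

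- lower: 0.300 − √(0.232² + 0.304²) = −0.08
- upper: 0.300 + √(0.287² + 0.082²) = 0.60

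That is wide, but usable.

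**Step 4: large samples.** Assume baseline 10% in both arms and Week 12 20% against 40%. The true marginal log odds ratio is ln(0.4/0.6) − ln(0.2/0.8) = 0.98. With baseline on both sides the interaction is about 1.2. It is about 1.0 without the covariate, and the Week 12 effect is about 1.05 with baseline as a covariate only.

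**Step 5: baseline as a covariate only (Weeks 4 and 12 as outcomes).** For the Week 12 cells alone, with placebo rate a and yFMT rate b,

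P(a 0/10 or 10/10 cell) = 1 − [1 − (1 − a)^10 − a^10][1 − (1 − b)^10 − b^10]

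With b = 40% this is 35%, 11% and 3% at a = 10%, 20% and 30%. In simulation of the full model, no finite Week 12 effect occurred in about 41-48%, 14-20% and 5% of trials. The placebo Week 12 rate drives this; the baseline rate hardly matters.

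**The case against.** The strongest reply is that the wording admits a benign reading. The span from baseline to Week 12 may only describe the period of change, and naming baseline status as a covariate suggests that Weeks 4 and 12 are the outcome rows. On that reading steps 1, 2 and 4 fall away and step 5 applies. This stands as a reading, but the text does not settle it, and failure remains frequent if the placebo rate is low.

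The second reply is that Fisher's exact test is already prespecified because of the sample size and always returns a p-value. That is true, but it is assigned a sensitivity role, no rule promotes it, and no effect estimate is planned with it. Penalisation and small-sample variance corrections can fairly be left to an analysis plan; the role of baseline and the primary estimate should not be ambiguous in the protocol.

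Three stronger readings are tempting and not supported.

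- A reader might infer that almost nobody will be an achiever at baseline. The entry rule is HbA1c or TIR, so someone with TIR above 70% can enter through HbA1c, and the baseline CGM window (section 2.4.2) coincides with insulin optimization. A low rate is plausible, but it is an assumption.
- A reader might blame the covariate itself. If constant, it simply drops out, and an infinite coefficient for it need not affect the treatment contrast. The causes are the empty baseline cell and sparse Week 12 cells.
- A reader might infer that a low baseline rate would usually destroy the treatment effect even with baseline as a covariate only. Step 5 shows otherwise.

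**Conclusion.** The point holds in limited form. The text leaves baseline able to act as outcome and predictor at once. On that reading, the primary interaction has no finite estimate in most trials if baseline achievement is 10% or less, and in about 12-57% at 20-30%; in large samples it is about 1.2 where 1.0 to 1.05 is right. On the covariate-only reading, the loss is about 5% of trials at placebo 30%, rising to 41-48% at 10%. All these figures rest on assumed achievement rates and a latent correlation of 0.5; only the 10 per arm and the model terms come from the document. Since this is a pilot and a Week 12 exact test is already planned, this is a correction worth making, not a flaw that undermines the trial.

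**What to change.** State as primary the between-arm difference in the proportion achieving the composite at Week 12, with non-responder imputation kept, a score-type 95% confidence interval (Newcombe or Miettinen–Nurminen) and the already planned Fisher's exact test. Under randomization this difference has the same expectation as the difference in change from baseline. Keep the GEE as supportive: Weeks 4 and 12 as the only outcome rows, baseline status only as a covariate, and a penalised fit if any cell is empty. Replace the open wording on when the covariate is used with a definite rule. Make the change before the unblinded interim review in section 2.9.

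The cost is wording only: no added participants, visits or measurements. The downside is a primary analysis that is not adjusted for baseline and has no longitudinal term; the supportive model supplies both where it can be fitted.

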#### 2.4.2. Run-in Period and Baseline Assessments (Day −17 to Day 0).

This period standardizes participants’ status prior to intervention and consists of two phases:

*Outpatient Phase* (Day −17 to −3): Participants will wear CGM and undergo insulin dose optimization. During this period, participants are instructed to follow a standardized diet according to the Chinese Diabetes Dietary Guidelines (2017). Dietary adherence is monitored through food records and regular follow-up communications via WeChat or outpatient visits. CGM data from this phase serves as the baseline for glycemic metrics, including TIR, TBR3.9, glucose management indicator (GMI), coefficient of variation (CV), and other metrics.

*Inpatient Phase* (Day −3–0): Participants are hospitalized for baseline assessments and bowel preparation:

(1) Baseline Assessments (Completed by Day −3) include:a. Demographics and clinical parameters: age, sex, T1DM duration, anthropometrics (height, weight, waist-to-hip ratio [WHR]), vital signs (blood pressure, pulse), and comprehensive medical/medication history;b. Glycemic and lipid profiles: fasting plasma glucose, 2-hour postprandial glucose via Mixed-Meal Tolerance Test [MMT], HbA1c, total cholesterol (TC), triglycerides (TG), low-density lipoprotein cholesterol [LDL-c], and high-density lipoprotein cholesterol [HDL-c];c. β-cell function and insulin sensitivity (fasting/stimulated 2-hour C-peptide during Mixed-Meal Tolerance Test [MMT 2h CP], estimated glucose disposal rate [eGDR]);d. Diabetic autoantibodies: Glutamic Acid Decarboxylase Autoantibodies [GADA], Insulinoma-associated antigen-2 autoantibodies [IA‑2A], Islet cell autoantibodies [ICA];e. Inflammatory markers: white blood cell count [WBC], High-Sensitivity C-reactive protein [hs-CRP], erythrocyte sedimentation rate [ESR], procalcitonin [PCT], and cytokines [TNF-α, IL-1β, IL-8, IFN-γ];f. Intestinal Barrier-Related Antibodies: Anti-Lipopolysaccharide [Anti-LPS], Anti-Occludin;g. Immune marker: Treg/Th17 ratio;h. Gut microbiome and serum metabolomics;i. Patient-reported outcomes (PROs): Simplified Chinese version of the EQ-5D-5L, Diabetes Distress Scale [DDS], Chinese version of the Hypoglycemia Fear Survey II-Worry Scale [CHFSII-WS];j. Laboratory safety indicators: liver and renal function.

Detailed protocols for all laboratory measurements, including sample processing, storage conditions, and analytical methods, are summarized in S2 File.

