### 2.5. Endpoints

The primary endpoint is change in the composite achievement rate of TIR > 70% and TBR3.9 < 4% at 3 months (Weeks 10–12) post-intervention compared to baseline (days −17 to −3 during the run-in period). Secondary efficacy endpoints included glycemic metabolism, β-cell function, insulin sensitivity, immunomodulation, Intestinal Barrier-Related Antibodies, inflammatory markers, gut microbiome and metabolites, PROs, lipid profile and TDD. The 1-month (Weeks 2–4) assessment is defined as a secondary endpoint to evaluate early glycemic changes. Feasibility endpoints include: (1) recruitment rate (proportion of screened participants enrolled); (2) retention rate (proportion of participants completing the 12-week follow-up); (3) intervention adherence (percentage of prescribed capsules consumed); and (4) acceptability (participant-reported tolerability and willingness to undergo treatment). Safety endpoints comprised the incidence of AEs (such as gastrointestinal symptoms, infection-related events, immune-related reactions, and allergic responses), as well as the incidence of serious AEs (SAEs, including severe hypoglycemia, diabetic ketoacidosis, hospitalization, disability, life-threatening events, or death). Detailed information is provided in Table 3.

**Table 3 pone.0343078.t003:** Study endpoints.

Primary endpoint	change in the composite achievement rate (TIR > 70% and TBR3.9 < 4%) at 3 months (Weeks 10–12) post-intervention
**Secondary endpoints**	change in the composite achievement rate (TIR > 70% and TBR3.9 < 4%) at 1 month (Weeks 2–4) post-intervention
	Changes in glycemic parameters at Week 4 and Week 12 post-intervention
	Changes in pancreatic β-cell function at Week 4 and Week 12 post-intervention
	Changes in insulin sensitivity indicators at Week 4 and Week 12 post-intervention
	Changes in TDD at Week 4 and Week 12 post-intervention
	Changes in infection and inflammatory markers at Week 4 and Week 12 post-intervention
	Changes in Intestinal Barrier-Related Antibodies at Week 4 and Week 12 post-intervention
	Changes in cellular immune indicators at Week 4 and Week 12 post-intervention
	Changes in lipid profile at Week 4 and Week 12 post-intervention
	Changes in gut microbiota composition and abundance at Week 4 and Week 12 post-intervention
	Changes in serum metabolomic profiles at Week 12 post-intervention
	Changes in PROs at Week 4 and Week 12 post-intervention
**Feasibility endpoints**	Recruitment rate
	Retention rate

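### Primary model: continuous baseline TIR, fixed in advance, would serve better than the probably sparse yes/no baseline target status (optional, modest gain)

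*Protocol article*

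**What the plan says.** - **Endpoint** (section 2.5, Table 3): "The primary endpoint is change in the composite achievement rate of TIR > 70% and TBR3.9 < 4% at 3 months", compared with the run-in window of Day −17 to −3.
- **Primary model** (section 2.10): "a generalized estimating equation (GEE) model with a binary distribution, logit link function, and an exchangeable correlation structure will be employed", with group, time and their interaction, and "with baseline composite achievement status as a covariates, as appropriate". Fisher's exact test at each time point is the sensitivity analysis.
- **Entry** (section 2.3, Table 1): "HbA1c between 7.0 to 14.0% (within past 3 months) or TIR < 70% (14-day CGM within the past month").
- **Baseline window** (section 2.4.2): "CGM data from this phase serves as the baseline for glycemic metrics, including TIR, TBR3.9". In the same window, "Participants will wear CGM and undergo insulin dose optimization".
- **Secondary outcomes** (section 2.10): each continuous outcome is adjusted for its own baseline value, so baseline TIR enters the mixed model for TIR but not the primary model.
- **Size and allocation** (sections 2.9 and 2.4.3): "a sample size of 10 participants per group was set", randomized 1:1 in permuted blocks. No stratification by starting TIR is described. One stated aim is to collect effect-size estimates for planning the pivotal trial.

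**The concern.** The trial recruits people whose glycemic control is off target and then adjusts the primary comparison for whether they were on target at baseline. Few are likely to be, so the covariate will have a very uneven split, and in some samples it will take one value only and drop out. It also discards the information that matters most for this endpoint, which is how far below 70% a participant starts. TIR of 65% and of 35% both count as off target.

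With 10 per arm, chance differences in starting TIR are likely, and a sparse yes/no covariate can correct little of them. The resulting estimate is meant to feed the planning of a larger trial. Separately, the qualifier closing the covariate clause leaves it undecided whether the covariate is used at all.

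**Working it through.** **1. What the plan supplies.** The size is 2 × 10 = 20, taken from guidance that "a pilot study for a future definitive trial with 90% power and a two-sided alpha of 0.05 typically requires approximately 10–25 participants per group". The protocol gives no responder rate, SD, baseline-to-Week-12 correlation or expected share on target at baseline. There is therefore no planned figure on this point to reproduce, and every size below rests on assumptions.

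**2. Can baseline status vary?** Anyone with TIR below 70% in the baseline window is off target by definition. Two routes still lead to being on target: entry through HbA1c, and a qualifying TIR from an earlier CGM within the past month followed by insulin optimization in the baseline window. If a share p is on target, the chance of nobody on target among 20 is (1 − p)^20:
- p = 0.04: 0.96^20 = 0.44
- p = 0.11: 0.89^20 = 0.10
- p = 0.13: 0.87^20 = 0.06

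Simulated entry mixes gave constant status in 9–46% of samples. I take this as roughly 10–45%. It would be 100% only if everyone had TIR below 70% in the baseline window.

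**3. Prognostic content.** For a continuous baseline with correlation r and a responder rate q, R² = (r·φ(z_q))² / (q(1 − q)).
- r = 0.4, q = 0.2: (0.4 × 0.280)² / 0.16 = 0.078
- r = 0.6, q = 0.3: (0.6 × 0.348)² / 0.21 = 0.207
- r = 0.3–0.7 with q = 0.1–0.5: 0.03 to 0.31

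This ignores selection at entry and the TBR component. With both included, and mixed entry (assumed: 35% of the source population above TIR 70%, HbA1c–TIR correlation −0.7, 75% meeting the TBR limit, r = 0.3–0.7 before selection), TIR explained 2.2–13.5% of outcome variance and status 0.6–5.2%.

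**4. Swap in large samples.** The information ratio is the squared Wald z for group with TIR divided by that with status, in Week 12 logistic models. At r = 0.65–0.80 it was 1.08–1.21 in one set of simulations and 1.04–1.17 in another. At r = 0.4–0.5 it was 1.02–1.04. Together this is about 2–20%.

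**5. Swap at n = 20.** Variance of the group effect with linear adjustment, under the mixed entry of step 3:

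| r | Status v none | TIR v none | TIR v status |
|---|---|---|---|
| 0.3 | 1.036 | 1.046 | 1.010 |
| 0.5 | 1.015 | 0.993 | 0.978 |
| 0.6 | 1.004 | 0.972 | 0.968 |
| 0.7 | 0.979 | 0.933 | 0.953 |

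The last column runs from a 1% loss to a 5% gain. Using both covariates gave 1.097, 1.038, 1.012 and 0.964 against none, which is worse than TIR alone at every r.

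Power in Firth-type analyses of Week 12 changed by +1 to +4 points at r = 0.5–0.8 and by about −1.5 at r = 0.3 (within simulation error). Other assumed settings gave 0 to about +7 points, the largest with a Monte Carlo error of about 2 points.

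**6. When status is constant.** The swap then acts as an addition. One covariate costs a factor 1 + 1/(20 − 4) = 1.0625, so TIR must explain 1 − 1/1.0625 = 5.9% to break even. With everyone below 70% at baseline, the variance ratios for TIR against none at r = 0.3, 0.5, 0.6 and 0.7 were 1.044, 1.034, 1.014 and 0.982.

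**7. Chance imbalance.** The SE of the difference in mean baseline TIR is SD × √(2/10). For an assumed SD of 12 or 15 this is 5.37 or 6.71 points. The chance that the arms differ by more than 5 points is then 35% or 46%.

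**The case against.** The best defence is that the plan follows its own rule. Each outcome is adjusted for its own baseline value, and for the composite that value is composite status. TIR is one component and says nothing direct about TBR3.9. This stands as a defence of validity. It does not make the yes/no version the more informative choice.

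A second objection is cost. In logistic fits at n = 20, adding TIR raised the median SE of the log odds ratio from 1.02–1.05 to 1.17–1.28, and rejection did not improve (8.6–10.6% without, 8.1–9.6% with). That compares TIR with no covariate, whereas the plan already spends a parameter on status. Part of the SE rise also reflects a different, conditional odds ratio. The objection does apply in samples where status is constant, as step 6 shows.

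Third, the inputs are absent from the protocol. Section 2.4.4 lets participants adjust insulin on CGM data throughout, so a high baseline-to-Week-12 correlation is not assured. The simulations also model Week 12 alone, not the repeated-measures GEE. Both limits stand.

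The article does not say whether the baseline reading is itself a response in the GEE. If it is, a covariate from the same window is tied to that row by construction, and TIR would not fully remove this. The point here does not rest on it.

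**Conclusion.** The point holds as an optional efficiency improvement. The primary model uses a coarse and probably sparse covariate although a better one is already recorded, and its wording leaves the covariate open. The expected gain is about 2–20% more information in large samples and 0 to a few points of power at n = 20. It may be nil if the correlation is weak (about 0.3). All of this depends on assumed correlation, SD, TBR pass rate and entry mix.

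Three stronger readings are tempting but unsupported:
- **That the entry criteria make baseline status constant.** The HbA1c route and the insulin optimization during the baseline window leave room for on-target participants, so status is sparse and not fixed.
- **That a known share of information, such as 8–21% or 2–4 of the 20 participants, is lost and can be recovered at no cost.** That range is a large-sample result on inputs the protocol does not give, and the results at n = 20 are much smaller.
- **That the planned analysis is biased or wrong.** Baseline status is a legitimate baseline covariate, Fisher's exact test is retained, and the pilot makes no power claim.

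**What to change.** In section 2.10, replace baseline composite status in the primary model with continuous baseline TIR from the Day −17 to −3 CGM (for example per 10 percentage points). Do not include both. Delete the qualifier, so that the covariate is settled before anyone sees unblinded data, including the interim review by the DMC. Keep baseline composite status as a descriptive table by arm, and keep Fisher's exact test as the sensitivity analysis.

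The cost is one line of text, with no new data and the same nominal number of parameters. The one small downside is that the odds ratio becomes conditional on baseline TIR instead of baseline status, which the report should state.
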